## Abstract

**Introduction:**

Osteoarthritis is a chronic pathology that involves multidisciplinary management. Self-management for patients is an essential element, present in all international guidelines. During the time of the spa therapy, the patient is receptive to take the advantage of self-management workshops.

The aim of this study is to assess the effects of 18 days spa therapy associated with a self-management intervention in patients with knee osteoarthritis in comparison with spa therapy alone on a priority objective, personalized and determined with the patient, chosen in the list of 5 objectives determined during the self-management initial assessment.

**Methods and analysis:**

Two hundred fifty participants with knee osteoarthritis will participate to this multicenter, prospective, randomized, controlled study. All patients will benefit 18 days of spa therapy and patients randomized in the intervention group will participate to 6 self-management workshops. Randomization will be centralized. The allocation ratio will be 1:1. Data analysts and assessor will be blinded. The primary outcome is the effectiveness of the educational workshops associated with spa therapy in comparison with spa therapy alone on a priority objective, measured by Goal Attainment Scaling (GAS). The secondary outcomes are disability, health-related quality of life, and pain intensity.

**Ethics and dissemination:**

Ethics were approved by the CPP *Sud-Méditerranée II*. The results will be disseminated in a peer-reviewed journal and disseminated at PRM, rheumatology, and orthopedics conferences. The results will also be disseminated to patients.

**Trial registration:**

Trial registration number NCT03550547. Registered 8 June 2018.

Date and version identifier of the protocol. Version N°6 of March 12, 2018.

## Introduction

Osteoarthritis (OA) is the most common diagnosis made by general practitioners in older patients, and OA is the most common arthropathy to affect the knee [1]. About 25% of adults aged > 55 years experience significant knee pain; half of these have radiographic changes of OA and a quarter have significant disability [2]. According to the World Health Organization (WHO), in 2020, chronic disease will be the main source of disability. This evolution is related to the increase in life expectancy due to improvements in medical technology [3]. Risk factors are multiple: heredity, overweight, and trauma (sports, professional and surgery) [4, 5]. All these factors interact with each other and may contribute to worsened pain and disability and reduced mobility. According to the first evaluation of the socioeconomic impact of osteoarthritis in France conducted in 1993, the estimated annual cost was slightly less than one billion euros [6]. In 2003, the annual cost was approximately 1.8 billion euros. Overall costs for osteoarthritis have thus increased by more than 80%, i.e. 8% per year [7].

With lack of any curative treatment, except prosthetic surgery, non-pharmacological treatment is essential [8]. OA is a chronic joint disease that involves multidisciplinary care. International guidelines such as from the Osteoarthritis Research Society International (OARSI) recommend a non-pharmacological intervention associated with pharmacological treatment for pain for people with knee OA. The self-management of the patient is an essential element in all international recommendations.

Non-pharmacological therapies are exercise programs, self-management education program, and weight loss if necessary [9–11]. Education and self-management have a positive impact on pain, function, exercise level, weight, quality of life, and treatment adherence [12].

The efficiency of spa therapy was also demonstrated in knee OA [13]. Mechanisms of action in spa therapy treatment are not fully understood but a combination of factors: mechanical, thermal, and chemical seems to be the most evident [14]. Spa therapy resorts, common in Europe, include a large sample of patients with different phenotypes from early to advanced OA stages. The spa treatment context could offer good conditions for behavioral modification and could be a special opportunity for self-management [15].

On the other hand, the synergic effect of a self-management program associated with spa therapy for the patients with OA is still debated The spa resort is the opportunity to meet and interact with other patients and benefit from multidisciplinary medical and paramedical support for ameliorating pain and disability [16].

The proposed study will address to the persons having spa therapy for OA. It will be a question of proposing to them a spa therapy of 18 days associated with a self-management intervention on a priority objective, personalized and determined with the patient, chosen in the list of 5 objectives determined during the educational initial assessment.

We aim to conduct a multicenter, prospective, randomized study to evaluate the effectiveness of a 6 personalized self-management workshops associated with a spa therapy journey of 18 days. The proposed educational activities will focus on key areas of leadership in the OA: knowledge and beliefs of the pathology, educational physical exercise, diet, management of pain, articular ergonomics, and medical devices. The objective looked for by these programs is a real modification of the lifestyle of the patients.

This study is aimed at people with knee OA. The main objective is to measure the impact of 18 days spa therapy associated with an educational intervention in patients with knee osteoarthritis on a priority objective, personalized and determined by the patient, chosen in the list of 5 objectives determined during the educational assessment.

The secondary objectives are to compare the groups in terms of pain, disability, and health-related quality of life.

## Methods

### Trial design

This is a multicenter, prospective, comparative, superiority randomized trial. The population will be randomized in 2 arms: experimental group of a 6 personalized self-management workshops associated with a spa therapy journey of 18 days versus spa therapy of 18 days alone (active comparator).

The design and conduct of this trial will adhere to the requirements of the Standard Protocol Items: Recommendations for Interventional Trials (SPIRIT Annex). The results will be reported in accordance with the CONSORT Statement for non-pharmacologic trials.

### Participants

We will recruit 250 participants, male and female, who are 50–75 years old with a diagnosis of mono or bilateral knee OA, in 6 spa therapy resorts, in France. All people already registered for STT will receive an information letter with study notification and eligibility criteria. The center is Clermont-Ferrand University Hospital associated with Dax and Saint-Paul-Lès-Dax spa center, Royat, Bourbon-Lancy, Chaudes Aigues, Aix-les-Bains,Evaux les Bains, and Balaruc spa centers. Patient recruitment potential among people with knee OA in spa therapy is important. Indeed, OA represents the main disease treated by spa therapy (250,000 per year in France). For people who meet the inclusion criteria, the research coordinator will perform the information and consent process and the physician will verify the inclusion criteria. The full description of the eligibility criteria for participants is provided in Table 1.

**Table 1 Tab1:** Eligibility criteria for participants

Inclusion criteria	− People, male or female, 50 to 75 years old − Mono or bilateral knee OA according to American College of Rheumatology (ACR) criteria − Pain on an 11-point NRS ≥ 30/100 − Written consent obtained − Health insurance cover
Exclusion criteria	− Contraindication to spa therapy − Unstable angina − Cardiac failure − Behavioral disorders or comprehension difficulties making assessment impossible − Inability to speak, write, or read French language

### Randomization and allocation concealment

Participants who meet inclusion criteria and agree to participate will be randomly assigned (1:1) to the experimental or comparator group using the REDCap software. The randomization sequence will be computer-generated by an independent statistician using permuted variable block sizes stratified by centers. The randomization process will be centralized at the coordinating office which will have no involvement in the enrollment, follow-up, or assessment of participants. Only the independent statistician have access to the randomization list and allocation concealment.

Access to the system is controlled for each investigator by an individual login/password and using a secured https connection. Participants also have paper files which are anonymized and only contain the participant’s unique identification code. These are stored in a dedicated storage unit in each center. Access to the complete final trial dataset will be restricted to the statistician of the *Secteur Biométrie et Médico-économie* who will analyze the study data for the purpose of report and publication.

### Interventions

Both groups will receive a spa therapy during 18 days. Only the experimental group will receive the personalized self-management workshops. The aim is to propose a reinforcement of the spa therapy effect through 6 self-management workshops. The STT and the self-management workshops will be personalized and designed by expert spa therapy physicians. Interventions have been designed by a specialist steering committee, standardized and reproducible for all centers. The steering committee consists of investigators, a spa therapist, physician, and physiotherapist and the university hospital’s medical team (physician, physiotherapist, adapted physical activity instructor). Self-management program has been implemented since 2018 in Dax thermal care facilities. It aims to make the patients able to improve their quality of life by an accurate comprehension of their particular situation and participation in six workshops dedicated to get the necessary skills. The workshops aim at better understanding of the disease, use of drug treatments, nutrition, joint protection, and physical activity. The self-management program has been patronized by the French Association for Thermal Research (AFRETh) and was agreed by Nouvelle Aquitaine Regional Health Agency (ARS). A personalized educational diagnosis allows the identification of personal goals to be achieved by the patient.

Meetings with all members of the steering committee are organized to obtain consensus on the therapeutic protocol describing precisely the content and the organization of the intervention taking into account the context and the expertise of the different centers involved in the study.

A flow of the participants through the study is provided in Fig. 1.

**Fig. 1 Fig1:**
[figure not shown]
Flow of the participants through the study

The Data Monitoring Committee (DMC) will be responsible for safeguarding the interests of trial participants, assessing the safety and efficacy of the interventions during the trial, and for monitoring the overall conduct of the clinical trial. The DMC will provide recommendations about stopping or continuing the trial to the Steering Committee (SC) of the trial. The SC will be responsible for promptly reviewing the DMC recommendations, to decide whether to continue or terminate the trial and to determine whether amendments to the protocol or changes in trial conduct are required.

The DMSC is an independent multidisciplinary group consisting of clinicians and a biostatistician that, collectively, have experience in the conduct, monitoring and analysis of randomized clinical trials. The members of the DMSC will be chosen among experts without conflicts of interest that could be perceived as inferring with the study.

This independent DMC will meet a first time at study initiation and then throughout the duration of the study at its own initiative or at the sponsor’s request and after 50% of inclusions.

The DMC will remain blinded for the allocation during analysis; however, the observation of differences in serious adverse events between the two groups may allow, for safety reasons, to unblind allocation groups.

### Self-care workshops

The main objective of the health education workshops will be to enable patients to acquire knowledge and competencies (attitudes, behavior) regarding their pathology and existing treatments. Each of the 6 health educational workshops will last between 1 h and 1 h and a half (Table 2). A multidisciplinary team will assure the educational interventions. To facilitate the workshops, different teaching tools and techniques will be used: paper board, thematic discussion, participative discussion, practical leaflets (Borg scale, deconditioning circle), exercise demonstration, feedback, and pain coping skills. The exchanges between the patients and the educative personals as well as the motivational communication will be the basic principles for every workshop.

**Table 2 Tab2:** Predefined objectives for each self-management workshop

Workshops	Objectives
Knowledge of the pathology	− Know the mechanisms of the OA and its risk factors, evolutionary modes and main current therapeutic strategies − Be able to speak usefully about OA and identify situations where it is necessary to see a doctor
Educational physical exercise practice	− Highlight the interest of the Adapted Physical Activity − Pacification and adaptation of physical activity to progress by knowing how to recognize the physical potential and the limits
Diet	− Diet in relation to the presence of knee osteoarthritis
Management of pain, fatigue, and the medical treatments	− Identify the relationship with the pharmacological treatments − Describe the non-pharmacological treatments for OA: psychological and physical
Articular ergonomics	− Allow for joint protection in everyday life − Better move by mobilizing the joint and protecting it during the movement.
Medical devices, an adaptation to the living conditions	− Foot orthoses, knee braces and technical helps.

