### Statistical considerations

#### Sample size estimation

According to the previous works presented in literature, we have estimated that a sample size of 105 patients per randomized group would provide 95% statistical power of highlighting an effect-size greater than 0.5 for a two-sided type I error at 5% for the primary outcome GAS T-score. Finally, a total of 250 patients (125 by group) will be considered to take into account lost to follow-up. With such sample size, a minimal absolute difference of 20% (50% versus 30%) can be shown for the secondary endpoint clinical improvement as defined in the thermarthrose [13] study for a power of 90%.

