#### Statistical analysis

Statistical analyses will be conducted using the Stata software (version 13, StataCorp, College Station, USA). A two-sided *p*-value of less than 5% will be considered to indicate statistical significance.

Concerning the primary outcome, the comparison between groups for univariate analysis will be analyzed using Student’s *t*-test or Mann-Whitney’s test. The normality will be studied by the Shapiro-Wilk test and the homoscedasticity using the Fisher-Snedecor test. Then, the analysis of the primary outcome will be completed by multivariable analysis using a linear mixed model to take into account: (1) fixed effects covariates determined according to univariate results and to clinical relevance (for example gender, age, analgesic treatments and season) and (2) center as random-effects (to measure between and within center variability). The normality of residuals will be studied as aforementioned. Intention-to-treat (ITT) analysis will be considered for the primary outcome, more precisely for all randomized patients except those without consent.

Other continuous endpoints (WOMAC, HEIQ, pain VAS, quality of life SF36, BMI) will be studied using the same statistical plan whereas the categorical parameters will be compared between groups with chi-squared or Fisher’s exact tests in univariate analyses and using generalized linear mixed model for multivariable analyses. For HEIQ and SF36 scores and pain VAS, the comparisons between groups will include in multivariable analyses the baseline values as independent parameters (fixed effects) as suggested by Vickers and Altman [18].

Longitudinal analyses concerning repeated measures at day 18 and months 3, 6, and 12 will be studied using random-effect models (linear or generalized linear), to take into account patient as random-effect (slope and intercept), nestled in center random-effect, while studying the fixed effects: group, time, and interaction *group x time*. According to clinical relevance, sub-group analyses depending the gender will be proposed after the analysis of interaction sub-group x randomization group in regression models (for repeated data or not).

Secondarily, a per-protocol analysis will be considered. A particular attention will be paid on number and duration of sessions and the type of intervention.

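### If the workshops are run in groups, the primary analysis and the 95% power make no allowance for correlation among experimental patients who share sessions

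*Protocol article*

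**What the plan says.** **Delivery.** The protocol article (Interventions) gives spa therapy to both arms and the six workshops to the experimental arm alone. Under Self-care workshops, a multidisciplinary team runs sessions of 1 to 1.5 hours in which "different teaching tools and techniques will be used: paper board, thematic discussion, participative discussion", among other tools. The same section names exchange between patients and educators as a basic principle of every workshop. No workshop group size appears. The only group size in the article, eight, is for the spa pool (SPA therapy treatment), which both arms use.

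**Analysis.** Under Statistical analysis, the primary outcome is first compared by a t-test or Mann-Whitney test. A linear mixed model follows, with "center as random-effects (to measure between and within center variability". A patient effect nested in centre appears only in the longitudinal models. No model has a term for workshop group or educator.

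**Sample size.** Under Sample size estimation, "a sample size of 105 patients per randomized group would provide 95% statistical power" for "highlighting an effect-size greater than 0.5", "for a two-sided type I error at 5% for the primary outcome GAS T-score". No ICC or design effect is mentioned. The total of 125 per arm allows for loss to follow-up.

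**The concern.** Patients who attend the same workshops share peers and educators, so their goal attainment may be correlated. Control patients have no workshops and so no matching source of correlation. The Discussion itself says that the success of behavioural treatments often depends on the skill and experience of those who deliver them.

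A centre random intercept does not deal with this. It is common to both arms, and randomisation is stratified by centre, so it represents what experimental and control patients at a resort share. It cannot represent differences between workshop groups that exist within a centre and in one arm only.

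If such correlation exists, the variance of the experimental mean is understated on the primary comparison. The test would then reject a true null too often, the confidence interval would be too narrow, and a valid test would have less power than stated.

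**Working it through.** **1. Reproduce the plan's figure.** Inputs from Sample size estimation: effect size 0.5, two-sided 5%, power 95%; 1:1 allocation from Randomization and allocation concealment. The exact t-test calculation gives 104.93, so 105 per arm, with power 95.0% (95.2% by the normal approximation). The stated figure is thus reproduced for independent patients and contains no allowance for clustering.

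**2. Formulas with clustering in one arm.** With m analysed trial patients per workshop group and n = 105 per arm:
- design effect in the experimental arm: DE = 1 + (m − 1) × ICC
- true variance divided by assumed variance: R = (1 + DE)/2
- type I error when grouping is ignored: 2 × [1 − Φ(1.96/√R)]
- power of a test with the correct standard error: Φ(0.5/√[(1 + DE)/105] − 1.96)

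**3. Results.** Both m and ICC are assumptions; the article gives neither.

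| m | ICC | DE | R | Type I error | Power at 105 per arm |
|---|---|---|---|---|---|
| 2 | 0.05 | 1.05 | 1.025 | 5.3% | 94.7% |
| 3 | 0.05 | 1.10 | 1.05 | 5.6% | 94.2% |
| 2 | 0.10 | 1.10 | 1.05 | 5.6% | 94.2% |
| 8 | 0.01 | 1.07 | 1.035 | 5.4% | 94.5% |
| 8 | 0.05 | 1.35 | 1.175 | 7.1% | 91.7% |
| 8 | 0.10 | 1.70 | 1.35 | 9.2% | 87.7% |

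Worked row (m = 8, ICC 0.05): √1.175 = 1.084, so the standard error is too small by that factor. 1.96/1.084 = 1.808, which gives 7.1%. √(2.35/105) = 0.1496, and 0.5/0.1496 − 1.96 = 1.382, which gives 91.7%. Simulating the ordinary t-test with 40,000 runs per setting gave a type I error of 7.2% at m = 8, ICC 0.05 and 9.2% at ICC 0.10. These figures are for the two-group test; the centre-only mixed model was not simulated.

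**4. Which m is plausible?** What counts is the number of trial patients per group, not the number of people in the room. Sample size estimation gives 125 experimental patients, Participants gives at least 6 resorts, and Trial status gives randomisation from March 2019 to December 2023, about 58 months. 125/6 = 20.8 per resort, and 20.8/58 = 0.36 per resort per month if spread evenly. Groups of eight trial patients would need recruitment in two or three batches per resort. Small groups are more likely, although uneven recruitment could produce some larger ones.

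**5. If nobody is lost.** With 125 analysed per arm, power at m = 8 and ICC 0.05 would be 95.4%. The type I error would stay at 7.1%, because it does not depend on n.

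**The case against.** The strongest objection is to the premise. Group delivery is inferred. The article calls the workshops personalised, stresses exchange between patients and staff, and refers to a separate therapeutic protocol for the organisation of the intervention. The remark that "The spa resort is the opportunity to meet and interact with other patients" describes the resort, which both arms attend, and is not evidence about workshop format. Nor can the pool's group size be carried over to the workshops. All this stands, and it makes the point conditional.

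The recruitment argument also stands: on average there are few experimental patients per resort at any time, so the larger effects in the table are the less likely ones.

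It could also be said that the full protocol or analysis plan may settle the matter. But the article does not leave the random effects open. It names centre for the primary model, and that named structure omits a level which discussion-based workshops in one arm would most naturally create.

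A reader might go further and infer that the primary intervals are too narrow, that the test is anti-conservative, or that 105 per arm is miscalculated. The documents do not support this. The first two need shared sessions and a positive ICC, neither of which is given, and the third is contradicted by the exact reproduction under independence.

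**Conclusion.** The point holds in conditional form. If experimental patients share workshop sessions and their outcomes are positively correlated within groups, the planned primary standard error would be too small and the 95% power too high. The direction is fixed; the size is not. At ICC 0.05 with two or three trial patients per group, which the recruitment figures make more likely, the type I error would be 5.3% to 5.6% and power 94.7% to 94.2%, a minor effect. With eight per group it would be 7.1% and 91.7% at ICC 0.05, and 9.2% and 87.7% at ICC 0.10. These figures assume equal group sizes, 105 analysed per arm and a normal approximation. The stated sample size is arithmetically correct for independent patients. The change is worth making because it is cheap and protects the primary test, and because the correlation may be impossible to assess later if group membership is not recorded.

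**What to change.** - Record in REDCap the workshop group each experimental patient attended: resort and session dates, and educator if known. Dates are needed because the article does not say that the same patients attend all six workshops together.
- If sessions are shared, add to the primary linear mixed model, alongside centre, a random effect for workshop group in the experimental arm only, with controls as singletons. Use small-sample degrees of freedom and base the primary inference on this model.
- If almost all groups hold a single trial patient, keep the centre-only model and report that this was so.
- State under Sample size estimation that the 95% power assumes no workshop clustering, and give the range above with its assumed m and ICC.

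The cost is a small addition to data capture and one model term, with no extra patients. The downside is a slightly wider interval, a stated power up to a few points lower over most of the range (about seven at m = 8, ICC 0.10), and a variance component that may be poorly estimated when groups are small.
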